# A comparison of three induction regimens using succinylcholine, vecuronium, or no muscle relaxant: impact on the intraoperative monitoring of the lateral spread response in hemifacial spasm surgery: study protocol for a randomised controlled trial

**DOI:** 10.1186/1745-6215-13-160

**Published:** 2012-09-08

**Keywords:** Hemifacial spasm, Microvascular decompression, Muscle relaxant, Succinylcholine, Vecuronium, Intraoperative monitoring, Lateral spread response

## Abstract

**Background:**

Surgical microvascular decompression (MVD) is the curative treatment for hemifacial spasm (HFS). Monitoring MVD by recording the lateral spread response (LSR) intraoperatively can predict a successful clinical outcome. However, the rate of the LSR varies between trials, and the reason for this variation is unclear. The aim of our trial is to evaluate the rate of the LSR after intubation following treatment with succinylcholine, vecuronium, or no muscle relaxant.

**Methods and design:**

This trial is a prospective randomised controlled trial of 96 patients with HFS (ASA status I or II) undergoing MVD under general anaesthesia. Patients are randomised to receive succinylcholine, vecuronium, or no muscle relaxant before intubation. Intraoperative LSR will be recorded until dural opening. The primary outcome of this study is the rate of the LSR, and the secondary outcomes are post-intubation pharyngolaryngeal symptoms, the rate of difficult intubations, the rate of adverse haemodynamic events and the relationship between the measurement of LSR or not, and clinical success rates at 30 days after surgery.

**Discussion:**

This study aims to evaluate the impact of muscle relaxants on the rate of the LSR, and the study may provide evidence supporting the use of muscle relaxants before intubation in patients with HFS undergoing MVD surgery.

**Trials registration:**

http://www.chictr.org/ ChiCTR-TRC-11001504 Date of registration: 24 June, 2011.

The date the first patient was randomised: 30 September, 2011.

## Background

Primary hemifacial spasm (HFS) is a disorder that causes frequent involuntary contractions in the muscles on one side of the face, due to a blood vessel compressing the nerve at its root exit zone (REZ) from the brainstem [1]. Numerous prospective and retrospective case series have confirmed the efficacy of microvascular decompression (MVD) of the facial nerve in patients with HFS with low rates of symptom recurrence and transient complications [1].

In 1985, Møller and Jannetta [2] showed that in HFS, stimulation of one branch of the facial nerve activates facial muscles innervated by another branch, thereby producing abnormal muscle responses (AMR). These AMR are known as the lateral spread response (LSR) and can be recorded from one muscle innervated by the superior branch of the facial nerve when the inferior branch is stimulated or vice versa (Figure 1). Due to the fact that the LSR disappears instantly in most patients when the offending vessel is moved off the facial nerve, monitoring the AMR can guide the surgeon during MVD, which results in a better post-operative outcome [3]. Although the practical value of the LSR disappearance as a method to evaluate MVD efficacy is still controversial [4,5], in most cases, LSR monitoring is an effective tool to predict outcome after MVD for HFS [6].

**Figure 1 F1:**
[figure not shown]
Schematic illustration shows the stimulation and recording electrodes.

However, an accurate estimate of the LSR rate is not yet known; the rate varies from 75% to 100% [7-14] between trials. Patients without the LSR would not benefit from this technology.

The reasons why the LSR is not detectable in some patients are unclear. Kong *et al*. hypothesised that the absence of the LSR was associated with the dosage of the muscle relaxant or the insertion site of the needle [11]; other researchers hypothesised that it was related to a process of denervation-reinnervation caused by preceding botulinum toxin injections [9]. However, these hypotheses have not yet been verified. While consulting the literature, we found that the muscle relaxants used in the various trials differed, which might be an important factor associated with the LSR rate. In most studies, short-acting muscle relaxants were used [1,7,9,10,13,15]. Sekula *et al*. [6] indicated that non-depolarising muscle relaxants should be used. While other studies described that muscle relaxants were used for intubation [4,14], they did not identify which muscle relaxants were used. Among the studies in the literature, several studies [11,13,16] performed the train of four (TOF) test to measure the degree of neuromuscular blockade and maintained the ratio at a level of 0.5 to 0.75.

### Succinylcholine

Succinylcholine (Sch) is an ultra-short-acting depolarising neuromuscular blocking agent (NMBA). This agent inhibits the action of acetylcholine at the neuromuscular junction. At a dose of 1 mg/kg, the onset time of Sch is 4 seconds; the time to 25% recovery is 10 minutes, and the time to 95% recovery is 12 to 15 minutes [17].

### Vecuronium

Vecuronium is an intermediate-acting non-depolarising neuromuscular blocking agent. This agent acts by competing for cholinergic receptors at the motor end-plate. At a dose of 0.1 mg/kg, the onset time of vecuronium is 2.3 minutes; the time to 25% recovery is 45 to 60 minutes, and the time to 95% recovery is 60 to 80 minutes [17].

The primary objective of this study is to evaluate the rate of LSR in HFS patients undergoing MVD under general anaesthesia with tracheal intubation, with succinylcholine, vecuronium, or no muscle relaxant. The secondary objectives are post-intubation pharyngolaryngeal symptoms, ease of intubation, haemodynamic responses and the relationship between the measurement of LSR or not, and clinical success.

## Methods

This is a randomised controlled study comparing the LSR rate in HFS patients undergoing MVD under general anaesthesia with tracheal intubation, and prior treatment with succinylcholine, vecuronium, or no muscle relaxant.

This study is a three-arm, randomised controlled trial. Participants fulfilling eligibility criteria were selected. Enrolled participants were randomly allocated to three parallel groups: the Succinylcholine, Vecuronium, or No Muscle Relaxant.

### Inclusion and exclusion criteria

Inclusion criteria: adult patients (American Society of Anesthesia (ASA) status I or II) (Table 1) [18] diagnosed with primary HFS and treated with MVD under general anaesthesia will be enrolled.

**Table 1 T1:** ASA physical status classification system

**Classification**	**Physical status**
1	A normal healthy patient.
2	A patient with mild systemic disease.
3	A patient with severe systemic disease.
4	A patient with severe systemic disease that is a constant threat to life.
5	A moribund patient who is not expected to survive without the operation.
6	A patient declared brain-dead whose organs are being removed for donor purposes.

Exclusion criteria: patients with: HFS secondary to aneurysms, tumours, or cysts; factors predictive of a difficult intubation; a BMI above 30 kg/m^2^; a history of allergy to muscle relaxants. Patients reporting any preoperative sore throat or hoarseness at history taking will be excluded.

All consenting patients fulfilling the inclusion criteria are randomised into three groups in a 1:1:1 ratio (G1, the Succinylcholine group; G2, the Vecuronium group; G3, the No Muscle Relaxant group). The flow chart of the present trial is shown in Figure 2.

**Figure 2 F2:**
[figure not shown]
**Trial flow chart.** *Rate of the LSR. **Post-intubation pharyngolaryngeal symptoms, ease of intubation and haemodynamic responses. ***Post-surgical symptoms of hemifacial spasm.

Patient demographic data will be collected for age, sex, duration of symptoms, location, history of botulinum toxin injections prior to MVD, and offending vessel.

Blinding: double blinding is not possible because of the muscle fasciculation caused by succinylcholine [19]. Outcome assessors will be blinded.

### Randomisation

Block randomisation was performed using a computer-generated list containing a sequence of letters, G1 referring to the Succinylcholine group, G2 referring to the Vecuronium group and G3 referring to the No Muscle Relaxant group. Block sizes vary with three, six or nine letters. Allocations were concealed in opaque, sealed envelopes. The envelope contains a number that is concealed as to the allocation. The list will be generated and kept by a person not involved in the study in the operating room. The number of envelopes matches the number of patients ready for the randomisation and follows the sequential numbers on the generated list.

### Outcome measures

The primary outcome is the intraoperative LSR rate.

All patients undergo orotracheal intubation in the supine position with the head and neck in neutral positions. Standard clinical monitoring is performed. After preoxygenation through a face mask for 4 min, anaesthesia is induced with propofol (target-controlled infusion (TCI) 4 to 6 μg/ml), sufentanil 0.3 to 0.5 μg/kg, midazolam 2 to 3 mg, and either succinylcholine 1 to 1.5 mg/kg (G1), vecuronium 0.1 mg/kg (G2), or no muscle relaxant (G3). Tracheal intubation is attempted 90 s after the administration. Intubation is always performed by an experienced anaesthetist using endotracheal tubes (Lo-Contour; Mallinckrodt, Athlone, Ireland) with an internal diameter of 7.0 mm for female patients and 7.5 mm for male patients. Mechanical ventilation is controlled, with end-tidal carbon dioxide being maintained at 30 to 40 mm Hg [17]. Anaesthesia is maintained using total intravenous anaesthesia (TIVA) with propofol and sufentanil.

After intubation, a bipolar subdermal needle electrode is inserted subcutaneously over the zygomatic branches of the facial nerve on the side of HFS with a 0.5 to 1 cm spacing. Another bipolar needle electrode is placed in the mentalis muscles for LSR recordings. Electrical stimulation, consisting of square-wave pulses (intensity: 5 to 15 mA; duration: 0.2 ms) and electromyographic (EMG) recordings, are filtered through a 30 Hz to 3 kHz band pass (gain: 500 mV/division; analysis time: 50 ms) (Axon Epoch 2000 Systems, Hauppauge, NY, USA). To avoid nerve fatigue, the LSR is evoked with a 2 min interval until dural opening.

The LSR is defined as the EMG response recorded from the mentalis muscle by electrical stimulation of the zygomatic branch of the facial nerve, usually with a latency of approximately 10 ms.

The secondary outcomes for this study are post-intubation pharyngolaryngeal symptoms, ease of intubation, haemodynamic responses, clinical success rates and its relationship to the measurement of LSR or not at 30 days after surgery, as described below:

1. Post-intubation pharyngolaryngeal symptoms are defined as hoarse or sore throat 24 h after extubation. The severity of the complaint is assessed on a 101-point numerical rating scale (0 = no discomfort, 100 = extreme discomfort).

2. The rate of difficult intubations is defined as an IDS score >5. The IDS (Table 2) is the sum of the seven following variables: number of tracheal intubation attempts, number of operators who attempted intubation, number of alternative techniques used, glottic exposure (as defined by the Cormack and Lehane classification [20]), intensity of lifting force (normal or increased) applied during laryngoscopy, necessity for external laryngeal manipulation, and position of the vocal cords (Table 2) [21].

3. The rate of adverse haemodynamic events is defined as hypotension and bradycardia and the need to administer ephedrine or atropine.

4. Clinical success is defined as HFS relief at 30 days after surgery.

**Table 2 T2:** IDS Score

**Parameter**	**Score**
Number of attempts > 1	N1
Number of operators > 1	N2
Number of alternative techniques	N3
Cormack grade	N4
Lifting force required	
Normal	N5 = 0
Increased	N5 = 1
Laryngeal pressure	
Not applied	N6 = 0
Applied	N6 = 1
Vocal cord mobility	
Abduction	N7 = 0
Adduction	N7 = 1

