### Statistical analysis

Double data entry will be done by assistants not participating in the study. Baseline characteristics will be described and compared for all three groups. All main analyses were based on the intention-to-treat patients.

The primary statistical analysis is performed at the end of the surgery. All three group comparisons will be conducted. LSR rates will be compared using the chi-square test and RR is assumed for the calculation. All the dichotomous (secondary) outcomes will be compared between the three treatment groups using the chi square (or Fisher’s exact) test. Continuous (secondary) outcome of the severity of the complaint will be compared using one-way ANOVA.

Statistical analyses will be carried out using the SPSS software (SPSS 18.0, Chicago, IL, USA). A *P* <0.05 will be considered statistically significant.

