### Treatment discontinuation

If intubating conditions are unsatisfactory due to poor muscle relaxation, the second anaesthetist in attendance could administer succinylcholine (1 mg/kg) to patients in the No Muscle Relaxant group, but all patients randomized need to be included in the analyses.

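### Difficult intubation is defined only as IDS >5, which names no rescue relaxant, so a rescued No Muscle Relaxant patient can be reported as not difficult

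*Protocol article*

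**What the plan says.** Ease of intubation is a declared aim. At the end of the Background (under Vecuronium) the article states: "The secondary objectives are post-intubation pharyngolaryngeal symptoms, ease of intubation, haemodynamic responses". Outcome measures makes this a yes/no outcome: "The rate of difficult intubations is defined as an IDS score >5". The score adds seven items: attempts, operators, alternative techniques, glottic view, lifting force, laryngeal pressure and vocal cord position. The operator item is worded as "number of operators who attempted intubation". Neither the text nor Table 2 lists a rescue drug or failure of the assigned induction.

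Treatment discontinuation sets the rescue rule. The trigger is "If intubating conditions are unsatisfactory due to poor muscle relaxation", and the action is that "the second anaesthetist in attendance could administer succinylcholine (1 mg/kg) to patients in the No Muscle Relaxant group". No other arm is named. The same sentence adds that "all patients randomized need to be included in the analyses".

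On testing, Statistical analysis says "All the dichotomous (secondary) outcomes will be compared between the three treatment groups", by chi-square or Fisher's exact test. It also says "All three group comparisons will be conducted", without stating whether that means pairwise tests.

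**The concern.** The rescue is triggered by poor intubating conditions, and the outcome is meant to measure intubating conditions. Yet the outcome has no item for the rescue, and the rescue is authorised in one arm only. That arm is also the one in which poor relaxation is most to be expected. A no-relaxant induction that failed for lack of relaxation could therefore enter the table as an easy intubation.

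The retention rule does not resolve this. It settles who is analysed, not what counts as an event.

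At stake is a secondary comparison that readers will use as a cost of omitting the relaxant, to be set against any gain in the lateral spread response. The error would run in favour of no relaxant.

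**Working it through.** **Inputs.** Items and cut-off are from Outcome measures and Table 2. Arm sizes are from Sample size calculation: 27 per arm evaluable, and 81/(1 − 0.15) = 95.3, rounded up to 96 recruited, or 32 per arm. The article gives no expected rate of difficult intubation, no rescue rate and no distribution of IDS totals, so there is no plan figure to reproduce for this outcome.

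**Can a rescued patient total 5 or less?** Take one extra attempt (N1 = 1), one operator (N2 = 0), no alternative technique (N3 = 0), increased force (N5 = 1), laryngeal pressure (N6 = 1) and adducted cords (N7 = 1). The second anaesthetist who gives the drug has not attempted intubation, so N2 stays 0. The sum before the Cormack item is 1 + 0 + 0 + 1 + 1 + 1 = 4. Table 2 does not say whether grade 1 scores 0 or 1, so both are shown.

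- Grade 1 view: 4 or 5. Not difficult on either scoring.
- Grade 2 view: 5 or 6. Difficult on the second scoring only.

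The remaining items give 4 grades × 2 × 2 × 2 = 32 combinations. Those totalling 5 or less are:

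| Situation | Grade 1 scored 0 | Grade 1 scored 1 |
|---|---|---|
| Rescue before any repeat attempt | 31 of 32 | 27 of 32 |
| One extra attempt | 27 of 32 | 20 of 32 |
| One extra attempt, rescue given one point as an alternative technique | 20 of 32 | 12 of 32 |

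These count combinations and are not probabilities.

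**Effect on the rate.** Each uncounted rescue lowers the arm's rate by 1/32 = 3.1 points (1/27 = 3.7). Suppose one patient of 32 in the No Muscle Relaxant arm has IDS >5 and all rescued patients score 5 or less. The plain rate stays at 1/32 = 3.1%. With 2, 3, 6 or 10 rescued, the rate of IDS >5 or rescue is 3/32 = 9.4%, 4/32 = 12.5%, 7/32 = 21.9% or 11/32 = 34.4%.

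**Effect on the test (illustrations, exact tests, 32 per arm).**

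- No IDS >5 event in the other two arms and every rescue at 5 or less: three-arm 0/0/3 gives p = 0.104 and 0/0/4 gives p = 0.0325 when rescues are counted. When they are not, p = 1.
- Against a single comparator, 0 v 4 gives p = 0.113, 0 v 5 gives 0.053 and 0 v 6 gives 0.024.
- If half of the rescues already exceed 5: with 4 rescues, three-arm p = 0.0325 counted against 0.33 (0/0/2) uncounted. With 6, pairwise p = 0.024 against 0.24 (0 v 3).
- With 1, 2 or 3 IDS >5 events in every arm, pairwise significance needs 7, 7 or 8 uncounted rescues: 1 v 8 gives p = 0.026, 2 v 9 gives 0.043 and 3 v 11 gives 0.032. That is 22% to 25% of the arm.

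**The case against.** The strongest reply is that the plan is coherent as a comparison of induction policies. One policy is no relaxant with succinylcholine in reserve; every randomised patient is analysed, and IDS >5 measures how hard intubation was under that policy. Failure of the assigned regimen is then a separate question, and any cut-off on a graded scale misses some cases. This stands as a reason to keep IDS >5 and the retention rule. It does not remove the problem that a rescue prompted by poor conditions can leave no trace in the only reported measure of those conditions.

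A second reply is that the scale already reacts to what triggers rescue: extra attempts, force, pressure and adducted cords all add points. That is true, and a reader who inferred that the IDS ignores poor relaxation, or that rescued patients always score as easy, would go beyond the document. Some will exceed 5.

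A third reply is that the alternative-techniques item is undefined and might give rescue one point, and that the cited scale may already say which attempt is scored. Both are possible. With that point the worked example becomes 5 or 6, yet totals of 5 or less remain available in 20 or 12 of 32 combinations. If the cited scale fixes scoring before rescue, that part of the fix merely confirms it.

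Finally, case-report fields and supportive analyses are commonly left to fuller documents. Their absence is not the point; the event definition and the one-arm rescue rule are both fixed here, and they fit together badly.

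**Conclusion.** The point holds, with limits. As written, a rescued No Muscle Relaxant patient can be classed as not difficult, and the resulting bias in this comparison can favour no relaxant. The size cannot be stated beyond 3.1 points per uncounted rescue at 32 per arm, because neither the rescue rate nor the share of rescued patients above 5 is given.

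A reader might infer from the contrast of p = 0.0325 with p = 1 that the planned test will give the wrong answer. The document does not support that: the contrast assumes no events in the other arms and no rescued patient above 5, and ordinary background rates require many more rescues. The pairwise figures also assume that pairwise tests are intended. Nor is the primary outcome definition or the sample size affected. This is a change that should be made to one secondary outcome, with medium confidence.

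**What to change.** 1. Keep IDS >5 as defined.
2. In a rescued patient, take view, lifting force, laryngeal pressure and cord position from the attempts before rescue, and still add later attempts to N1, so that rescue cannot lower the score.
3. Record rescue relaxant (yes/no and time) in every arm, although only one arm has it authorised.
4. Report, side by side, the plain IDS >5 rate, the number rescued by arm, and a pre-specified supportive rate of IDS >5 or rescue relaxant. Date the change and fix it before any comparison by arm.

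The cost is one case-report field, if it is not already collected, and its recovery from anaesthetic records for the more than 30 patients included by the date of the Trial status section. Pre-rescue scores for those patients may be harder to recover.

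The composite has its own weakness. It adds events mainly in the one arm where rescue is authorised. The trial is not double-blind, so a precautionary rescue is possible and would count as difficult. It must therefore sit beside IDS >5 and not replace it.

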### Sample size calculation

We performed a pilot study of the LSR rate (following the same protocol as the proposed study) before writing the protocol. According to the results of our preliminary study, the Vecuronium group percentage is assumed to be 60%, the Succinylcholine group percentage is assumed to be 70%, and the No Muscle Relaxant group percentage is 100%. Effect size is assumed 0.4 corresponding to our preliminary result. A sample size of 27 patients for each study group with an allocation ratio of 1:1:1 for a total of 81 patients is required to achieve 90% power (alpha at 0.05) to detect a difference among the groups in the primary end-point variable (LSR rate) (G*Power 3.1.2 software). Allowing for a drop-out rate of 15% per group, we decided to recruit 96 participants.

### Statistical analysis

Double data entry will be done by assistants not participating in the study. Baseline characteristics will be described and compared for all three groups. All main analyses were based on the intention-to-treat patients.

The primary statistical analysis is performed at the end of the surgery. All three group comparisons will be conducted. LSR rates will be compared using the chi-square test and RR is assumed for the calculation. All the dichotomous (secondary) outcomes will be compared between the three treatment groups using the chi square (or Fisher’s exact) test. Continuous (secondary) outcome of the severity of the complaint will be compared using one-way ANOVA.

Statistical analyses will be carried out using the SPSS software (SPSS 18.0, Chicago, IL, USA). A *P* <0.05 will be considered statistically significant.

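### The plan does not say which test decides the primary outcome: the trial is sized on one three-arm test, but the analysis section appears to allow three unadjusted pairwise tests

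*Protocol article*

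**What the plan says.** The Outcome measures section names one primary endpoint: "The primary outcome is the intraoperative LSR rate".

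The Sample size calculation section assumes LSR rates of 60% (vecuronium), 70% (succinylcholine) and 100% (no muscle relaxant), and adds "Effect size is assumed 0.4 corresponding to our preliminary result". From these it derives 27 patients per arm, 81 in all, for 90% power at alpha 0.05 "to detect a difference among the groups in the primary end-point variable (LSR rate)". Recruitment is raised to 96 for 15% drop-out.

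The Statistical analysis section says of the primary outcome: "All three group comparisons will be conducted. LSR rates will be compared using the chi-square test and RR is assumed for the calculation". Its only threshold is P "<0.05 will be considered statistically significant". It gives no order of testing, gate or adjustment.

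**The concern.** The design spends alpha once, on a test of any difference among three arms. The analysis section seems to allow three tests of the same endpoint at that level. Three pairs can be formed from three arms, and a relative risk (RR) compares two groups, so pairwise results look intended. The trial's stated aim, to inform the choice of induction regimen, also needs to know which regimen differs.

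If any pairwise P below 0.05 can be reported as the primary finding, the trial has three chances of a false claim and its error rate is not the 5% behind the sample size. If only the three-arm test counts, the error rate is right but a significant result does not identify the regimen. Either way, a reader cannot tell in advance what would make the trial positive.

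**Working it through.** **1. The plan's own sample size.** Inputs, from the Sample size calculation section: rates 0.60, 0.70 and 1.00; w = 0.4; alpha 0.05; power 90%; drop-out 15%.

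- Mean rate: (0.60 + 0.70 + 1.00)/3 = 0.7667.
- Effect size: w = √{mean of (pᵢ − p̄)² / [p̄(1 − p̄)]} = √(0.02889/0.17889) = 0.402, which agrees with the stated 0.4.
- Noncentral chi-square with 2 df and w = 0.4: N = 80 for 90% power, rounded up to 81 for three equal arms. Power at 81 is 90.7%.
- Drop-out: 81/0.85 = 95.3, rounded up to 96, or 32 per arm.

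Every stated figure reproduces with the three-arm, 2-df test. That is the test the trial was sized on.

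**2. Error rate if any pairwise test counts.** Assume all three arms share one true rate. Enumerate every outcome of three independent binomials with n per arm, and apply chi-square tests without continuity correction:

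- pair with a and b responders: X² = 2n(a − b)² / [(a + b)(2n − a − b)], 1 df, at 0.05;
- three arms: X² = Σ n(p̂ᵢ − p̄)² / [p̄(1 − p̄)], 2 df, at 0.05.

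Ungated means that any pairwise P below 0.05 counts. Gated means that pairs are read only if the three-arm test is significant.

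| Shared rate | Ungated, n=27 | Gated, n=27 | Ungated, n=32 | Gated, n=32 |
|---|---|---|---|---|
| 0.50 | 10.2% | 5.6% | 14.4% | 5.4% |
| 0.60 | 11.2% | 5.3% | 13.4% | 5.1% |
| 0.70 | 13.1% | 5.0% | 12.4% | 5.1% |
| 0.80 | 13.6% | 4.7% | 12.1% | 5.0% |
| 0.90 | 12.7% | 3.4% | 13.5% | 4.1% |
| 0.95 | 5.8% | 1.6% | 8.0% | 2.1% |

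Two cross-checks: the normal approximation for three pairwise comparisons of three means gives 12.2%, and three independent tests would give 1 − 0.95³ = 14.3%.

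**3. Error rate if only the two relaxant arms are equal.** At 70/70/100% or 60/60/100% only one pairwise null is true. It is rejected 4.7–5.6% of the time (n = 27 or 32), with or without the gate. There is no inflation here.

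**4. Power cost of the gate** (other arms as planned at 60% and 70%). The 95% and 90% rates are my assumptions; the plan gives only 100%.

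| Rate without relaxant | n | Vecuronium vs none: ungated → gated | Succinylcholine vs none: ungated → gated |
|---|---|---|---|
| 100% (plan) | 27 | 99.89% → 99.70% | 97.98% → 97.80% |
| 95% (assumed) | 27 | 93.0% → 85.4% | 74.7% → 70.3% |
| 90% (assumed) | 27 | 77.2% → 63.1% | 48.7% → 42.0% |
| 95% (assumed) | 32 | 95.7% → 91.8% | 80.6% → 78.6% |
| 90% (assumed) | 32 | 82.8% → 72.1% | 53.3% → 48.7% |

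At the plan's rates and n = 27, succinylcholine vs vecuronium has 12.1% power either way.

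**5. The gate against a Bonferroni split at n = 27.** Succinylcholine vs none at the plan's rates: 97.8% gated, 86.4% with Bonferroni. At an assumed 90% without relaxant: 63.1% against 56.9% (vecuronium vs none) and 42.0% against 26.5% (succinylcholine vs none).

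**The case against.** The strongest reply is that the article never says three pairwise tests are each run at 0.05. The disputed phrase can also mean one comparison of all three groups. Neighbouring sentences on baseline and secondary outcomes use that sense, and the only place that attaches alpha to the primary endpoint speaks of a difference among the groups. An RR can be reported as an estimate beside a three-arm test. On this reading the primary error is about 5%, and what is missing is a follow-up rule that a condensed article may leave to the analysis plan.

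Much of this stands. A reader might infer that the plan fixes ungated pairwise testing and so has an 11–14% error rate as a matter of fact. The document does not support that, because its wording is ambiguous. Nor does the inflation hold generally. It needs all three arms equal, it is 6–8% at a shared rate of 95% (inside the 75–100% range the Background quotes), and it vanishes when only the relaxant arms are equal, the pattern nearer the plan's own assumptions. Pairwise Fisher tests would also lower the ungated error, to about 2–8% at n = 27 or 32 for shared rates of 50–90%, but the article names chi-square for the primary outcome.

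A reader might also infer that gating is free. That is true only near the assumed 100% rate without relaxant.

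What does not stand is that nothing is wrong. The section does fix comparisons, test, effect measure and threshold for the sole primary outcome. Following them on their more natural reading gives more than 5% error. On the other reading, the regimen that differs cannot be identified.

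**Conclusion.** The point holds in a conditional form. The sample size section rests on one three-arm test at 0.05, the analysis section calls for comparisons that read most naturally as pairwise, and neither names the deciding result. If any pairwise P below 0.05 counts, the chance of a false claim is 11.2–13.6% for shared rates of 60–90% at 27 or 32 per arm. If the three-arm test decides, it is about 5%.

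These figures assume uncorrected chi-square tests, equal arm sizes and, for the inflation, no true difference between any arms. This is worth correcting because it determines what may be claimed on the only primary endpoint. It falls short of a defect that must be fixed, because the inflation depends on one reading of an ambiguous sentence and on one null pattern.

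**What to change.** In Statistical analysis, state that the primary test is the 3×2 chi-square (2 df) at 0.05, and that the three pairwise comparisons are each tested at 0.05 only if it is significant. Report each pairwise risk difference or RR with its 95% confidence interval.

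With three arms this is a closed procedure. If any two pairwise nulls are true, all three arms are equal, so the three-arm test covers every such combination and alpha need not be split. With all arms equal, the enumerated error is 3.4–5.3% at shared rates of 60–90%. It reaches 5.6% at a shared rate of 50%, because the counts are discrete.

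The change is one sentence, needs no further patients and uses the test the trial was sized on. Its price is power if the rate without relaxant falls below 100%, as tabulated above. The extra power of ungated tests is bought with the inflated error, and at 27 per arm the gate costs less than a Bonferroni split in the comparisons shown.

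### The article plans only an unadjusted comparison of LSR rates, so a chance imbalance in prior botulinum toxin, a suspected cause of an absent LSR that is recorded at baseline, would stay in the pairwise differences

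*Protocol article*

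**What the plan says.** All references are to the protocol article.

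- **Statistical analysis.** For the primary outcome, "LSR rates will be compared using the chi-square test". The section announces comparisons among all three groups. Baseline characteristics are to be described and compared, but no stratified or adjusted analysis is stated.
- **Background (after Figure 1).** Several explanations for an undetectable LSR are reported: relaxant dosage, needle insertion site and, from other researchers, that "it was related to a process of denervation-reinnervation caused by preceding botulinum toxin injections". The text adds that none has been verified.
- **Methods (after Figure 2).** The baseline data include "history of botulinum toxin injections prior to MVD".
- **Randomisation.** Blocks of three, six or nine are used. No stratification factor is named.
- **Sample size calculation.** The assumed LSR rates are 60% (vecuronium), 70% (succinylcholine) and 100% (no relaxant). "Effect size is assumed 0.4 corresponding to our preliminary result". The result is "A sample size of 27 patients for each study group with an allocation ratio of 1:1:1 for a total of 81 patients", raised to 96 for drop-out.

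**The concern.** Of the explanations listed in the Background, prior botulinum toxin is the only one that is a patient characteristic fixed before randomisation. It is therefore the one that a stratified analysis could take into account at no cost in data. As the article stands, the toxin history would appear in a baseline table and nowhere else.

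Arms of 27 to 32 patients can differ noticeably in such a factor by chance. If the toxin does suppress the LSR, the imbalance passes straight into the difference between arms. The contrast of either relaxant with no relaxant is planned at 30 to 40 points and can absorb this. The contrast between the two relaxants is planned at 10 points and cannot absorb it easily. If the baseline table showed an imbalance, the article gives no planned response, and any adjustment chosen then would be post hoc.

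**Working it through.** **Inputs from the article:** LSR rates of 60/70/100%, effect size 0.4, alpha 0.05, power 90%, 27 per arm (81 in total), 96 recruited (32 per arm).

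**Assumptions, because the article gives no figures:** share previously injected 10%, 25% or 50%; odds ratio for LSR in injected against uninjected patients 1, 0.5, 0.25 or 0.1; a weaker set of rates, 65/70/90%.

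**1. The plan's own figure.** The mean rate is (0.60 + 0.70 + 1.00)/3 = 0.767.

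w² = [(0.167² + 0.067² + 0.233²)/3] / (0.767 × 0.233) = 0.0289/0.1789 = 0.161, so w = 0.402.

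This agrees with the stated 0.4. A noncentral chi-square with 2 df and noncentrality N × 0.16 needs N = 80 for 90% power, or 81 in equal arms (power 90.7%). Then 81/0.85 = 95.3, rounded up to 96. The sample size reproduces.

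**2. Power of the overall test**, unadjusted against stratified by toxin history (10,000 simulated trials per scenario):

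| Rates | Odds ratio | Unadjusted | Change with stratification |
|---|---|---|---|
| 60/70/100%, 27 per arm | 1 to 0.1 | 99.7–99.9% | −0.1 to +0.1 points |
| 65/70/90%, 27 or 32 per arm | 1 or 0.5 | 52–63% | about −1 to 0 points |
| same | 0.25 | same range | 0 to +3 points |
| same | 0.1 | same range | +4 to +10 points |

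Simulated power at the planned rates exceeds the 90.7% of step 1 because an arm at 100% has no binomial variation, so the statistic varies less than the formula supposes.

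**3. Size of a chance imbalance.** With 25% injected and 27 per arm, the standard deviation of the between-arm difference in toxin history is √(2 × 0.25 × 0.75/27) = 0.118; with 32 per arm it is 0.108. Take a split of 10, 7 and 4 injected patients. The extreme arms differ by 6/27 = 22 points, about 1.9 standard deviations for a given pair. The shift in LSR difference is 6/27 times the gap in LSR rate between uninjected and injected patients, at an overall rate of 76.7%:

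| Odds ratio | Uninjected / injected LSR | Shift, 10/7/4 split | Shift, 1-SD imbalance (0.118 × gap) |
|---|---|---|---|
| 0.5 | 80% / 67% | 0.222 × 0.13 = 3 points | 1.5 points |
| 0.25 | 84% / 56% | 0.222 × 0.28 = 6 points | 3.3 points |
| 0.1 | 88% / 42% | 0.222 × 0.46 = 10 points | 5.4 points |

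**4. Type I error of the unadjusted test.** Averaged over all randomisations it is 4.5% to 5.5%. Given the 10/7/4 split it is 5.0%, 5.7% or 6.8% for odds ratios of 0.5, 0.25 or 0.1. Given a more extreme 11/7/3 split it is 5.6%, 7.3% or 11.7%.

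**5. Precision of the succinylcholine–vecuronium difference.** Unadjusted, the standard error is √[(0.70 × 0.30 + 0.60 × 0.40)/27] = 0.129. Stratifying brings it to about 0.11 to 0.12 if the odds ratio is 0.1 and 30% to 50% are injected. With an odds ratio near 1 there is no gain.

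**The case against.** The strongest reply is that nothing here is an error. Under randomisation the unadjusted chi-square is valid, its error rate already includes chance imbalance, and it matches the test used for the sample size. All of that stands. It is also fair that the analysis plan is not shown and may contain a supportive adjusted analysis, and that the planned baseline comparison would make an imbalance visible.

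A reader might infer that the plan gives up power. The documents do not support this. At the planned 60/70/100% there is no power left to recover. If every patient without relaxant shows the LSR, toxin history can have no effect in that arm. Gains of 4 points or more for the overall test appear only when the no-relaxant rate is set below 100% and the toxin effect is very strong.

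A reader might also take botulinum toxin for an established or leading cause. The Background attributes the idea to other researchers, lists it beside relaxant dosage and needle site without ranking them, and calls all of them unverified.

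What the reply does not remove is the exposure of the pairwise estimates in the one trial that is run. Validity on average does not help the reader of a succinylcholine–vecuronium difference from arms that happen to differ in toxin history.

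**Conclusion.** The point holds as an inexpensive improvement in robustness, not as a flaw that invalidates the primary test. A marked but plausible imbalance could move a pairwise LSR difference by roughly 3 to 10 points, against a planned gap of 10 points between the relaxants. At the upper end that could cancel the gap or about double it. A one-standard-deviation imbalance would move it by about 1.5 to 5 points.

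These sizes rest on an assumed 25% injected and odds ratios from 0.5 to 0.1; the article gives neither. If the toxin has no effect on the LSR, there is no shift to correct. Stratification would not make the 10-point contrast well powered either: its standard error stays at about 11 points or more at 27 per arm.

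**What to change.** Pre-specify, before any comparison of LSR by arm is looked at, a Cochran-Mantel-Haenszel analysis of LSR by arm stratified by prior botulinum toxin (yes/no), with Mantel-Haenszel risk differences and confidence intervals for the three pairs. Report it alongside the unadjusted chi-square, and state in advance which of the two is decisive so that there is no choice afterwards. Do not use ordinary logistic regression for the adjustment: an arm at or near 100% produces separation and the estimates may not exist.

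If an analysis plan already contains this, a cross-reference is enough.

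The cost is wording only. The variable is already collected, and neither randomisation nor sample size changes, which matters because recruitment has begun. If toxin history turns out not to be prognostic, the stratified test gives up about 1 point of power or less. Any claim of a power gain for the overall test (about 4 to 10 points) should be made conditional on a no-relaxant rate below 100% and an odds ratio of about 0.1.
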